## Methods

### Study design

This is a non-randomised, uncontrolled, open-label longitudinal interventional pilot study, designed in line with recommendations from the Rome foundation paediatric subcommittee on pharmacological clinical trials in children with FC.^37^ The protocol is designed in alignment with the Standards for Reporting Interventions in Clinical Trials of Acupuncture.^38^ Expected recruitment phase is June 2025 to January 2026. A schematic depiction of the study design is shown in figure 1.

**Figure 1 F1:**
[figure not shown]
Schematic depiction of study design. Participants will receive eight acupuncture sessions over 10 weeks. At each session, symptoms and adverse events over the previous week will be recorded. Participants will complete surveys at five time points, including the validated PedsQL 4.0 Generic Core Scale and 3.0 Gastrointestinal Symptoms Scale and module, and questions monitoring adverse events, treatment satisfaction and school absence. After the baseline eligibility check, participants will visit the research nurse for five study visits, allowing for assessment of primary and secondary endpoints. The study visits at t=0, t=3, t=6 and t=10 will take place after the acupuncture sessions.

### Participants

Research subjects will be selected based on a diagnosis of FC according to the Rome IV criteria (table 1).

### Sample size calculation

This feasibility pilot study evaluates an intervention protocol not previously studied. A sample size of 18 patients was deemed sufficient to assess the primary objective, based on consultation with a statistician.^39 40^ The sample size calculation considers a significance level of alpha=0.05, power of 0.8, estimated feasibility of 0.9, and a lower bound of 0.7 for study exclusion. This sample size minimises patient exposure while providing enough data to inform the future RCT.

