**Methods and analysis:**

Prospective, non-randomised, open-label pilot study in children with FC (6–18 years). Participants will undergo eight acupuncture sessions over 10 weeks. Concurrent pharmacological treatment with polyethylene glycol (≥0.2 g/kg/day) will continue as initiated prior to enrolment. The primary endpoint is feasibility, defined by an attrition rate of ≥70%. Secondary feasibility endpoints include consent rate, patient/parent satisfaction and personnel requirements. Safety will be assessed by systematic monitoring of adverse events. Efficacy endpoints include treatment success, defined as no longer meeting the Rome IV criteria for FC at the end of the intervention period, as well as defecation frequency, stool consistency, painful defecation, faecal incontinence frequency, abdominal pain, medication use and quality of life, based on a previously published core outcome set.

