### Outcomes

#### Primary outcome

##### Feasibility

Attrition rate, defined as the percentage of participants completing the study protocol. The intervention will be considered feasible if ≥70% of participants complete the study while attending ≥75% of acupuncture sessions.

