### Statistical analysis

Continuous data will be presented as mean±SD if normally distributed and as median with IQR otherwise. Categorical data will be presented as proportions. The 95% CI will be calculated for all primary and secondary parameters, with significance set at α=0.05. The primary outcome, attrition rate, is defined as the proportion of participants completing the study. Attendance at 100%, ≥75% and ≥50% of acupuncture sessions will be reported. Feasibility is confirmed if ≥70% of participants complete the study while attending ≥75% of sessions, informing a future RCT design. Secondary feasibility outcomes include consent rate, satisfaction and personnel capacity. Consent rate is the proportion of approached participants who provided consent, with age distribution reported as mean±SD or median (IQR). Reasons for non-participation will be described. Satisfaction scores (5-point Likert scale) at weeks 6, 10 and 14 will be summarised, visualised with bar plots and analysed descriptively. Personnel requirements will be summarised.

A table will summarise acupuncture points. Safety analysis includes AE frequency. Efficacy, assessed as the proportion no longer meeting Rome IV criteria, will be analysed using McNemar’s test. Due to the study design, no efficacy claims can be made without a control group.

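### The stated 5% alpha and 80% power describe neither the n=18 design nor the rule that decides feasibility (observed completion of at least 70%)

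*Protocol article*

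**What the plan says.** Under Sample size calculation, the article states that "A sample size of 18 patients was deemed sufficient to assess the primary objective" on a statistician's advice with two references, and that the calculation "considers a significance level of alpha=0.05, power of 0.8, estimated feasibility of 0.9, and a lower bound of 0.7 for study exclusion". It names no test, no formula and no sidedness.

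Under Primary outcome, the decision rule is: "The intervention will be considered feasible if ≥70% of participants complete the study while attending ≥75% of acupuncture sessions". Statistical analysis repeats it: "Feasibility is confirmed if ≥70% of participants complete the study while attending ≥75% of sessions". That section also promises 95% confidence intervals for primary and secondary parameters and sets significance at 0.05. Neither place makes the verdict depend on the interval or on a test.

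The Introduction makes the RCT conditional on this verdict. The body calls the endpoint attrition rate but defines it as the percentage who complete. The abstract says: "The primary endpoint is feasibility, defined by an attrition rate of ≥70" per cent.

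**The concern.** The sizing and the decision rule treat 70% in opposite ways. In the sizing it is "a lower bound of 0.7 for study exclusion", the unacceptable value to be distinguished from an expected 0.9. In the decision it is the pass mark. A rule that passes any observed rate at or above a boundary will pass a true rate at that boundary about half the time, so the quoted alpha cannot belong to it.

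Feasibility is the only primary endpoint and the go/no-go for the RCT. A reader who sees 5% alpha and 80% power next to a feasible verdict will take it that completion has been shown to exceed 70%. The rule as written cannot show that.

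**Working it through.** **Inputs.** n = 18, alpha = 0.05, power = 0.80, p1 = 0.90, p0 = 0.70 (Sample size calculation); pass if the observed proportion is at least 0.70 (Primary outcome; Statistical analysis).

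**1. Reproducing 18.** Two-sided Wald formula, variance at p1:

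n = (1.960 + 0.842)² × 0.9 × 0.1 / 0.2² = 17.66, rounded up to 18. Nominal power at n = 18 is 80.7%.

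Other common formulas with the same inputs do not return 18:

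| Formula | One-sided | Two-sided |
|---|---|---|
| Wald, variance at 0.9 | 14 | **18** |
| Score (null variance 0.21 in the alpha term) | 26 | 34 |
| Score with continuity correction | 31 | 38 |
| Arcsine | 24 | 30 |

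The Wald version leaves out the larger variance at the null (0.7 × 0.3 = 0.21 against 0.9 × 0.1 = 0.09).

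**2. What n = 18 delivers.** With X ~ Binomial(18, p), type I error is P(X ≥ r | 0.7) and power is P(X ≥ r | 0.9):

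| Cutoff r | Type I error | Power |
|---|---|---|
| 17/18 | 1.4% | 45.0% |
| 16/18 | 6.0% | 73.4% |
| 15/18 | 16.5% | 90.2% |
| 13/18 (the rule) | 53.4% | 99.4% |

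No row meets both targets. Which of the first two applies depends on the test:

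- An exact 5% test, one- or two-sided, needs 17/18; so does a two-sided score test (z = 2.26 at 17, 1.75 at 16).
- A Wald 95% lower limit above 0.70 needs 16/18: 0.889 − 1.96 × √(0.889 × 0.111 / 18) = 0.744. At 15/18 the limit is 0.661. A one-sided score test also uses 16/18.

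For scale, the smallest n at which an exact one-sided 5% test has at least 80% power is 28 (cutoff 24: alpha 4.7%, power 85.8%).

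**3. The rule in use.** 0.70 × 18 = 12.6, so at least 13 of 18 must complete with the required attendance. P(X ≥ 13):

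| True completion | Probability of a feasible verdict |
|---|---|
| 0.60 | 20.9% |
| 0.65 | 35.5% |
| 0.70 | 53.4% |
| 0.90 | 99.4% |

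At exactly 13/18 the exact (Clopper–Pearson) 95% interval is 47% to 90%, so a bare pass is compatible with a true rate well below 70%.

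**The case against.** A reader might infer that the authors miscalculated and that the stated test has 45% power, not 80%. The documents do not support that. The article names no test, 18 follows correctly from a recognised approximation, and the formula and sidedness may be given in the full protocol, which is not shown. The 45% belongs to a test held exactly to 5% and is partly an effect of discreteness: at n = 19 the exact test (cutoff 17) has alpha 4.6% and power 70.5%. At n = 18 power is 45% or 73%, depending on the test. The fair criticism is that the approximation is poor at this size.

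It can also be said that a pilot may properly use a point-estimate threshold for progression, and that a 95% interval is already promised. Both are true. But this article attaches alpha and power to its design, and the interval plays no part in the decision. The contradiction lies between two printed statements, so an unseen document could explain it but would not remove it.

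The abstract might be read as counting the loss of 70% of children as success. The body's definition shows that completion is meant. It is a labelling error and has no bearing on the error rates.

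**Conclusion.** The point holds. The stated alpha of 0.05 and power of 0.8 are not properties of the n = 18 design under any cutoff, nor of the rule that decides feasibility. That rule accepts the value the trial was sized to exclude, with a 53% chance of passing at a true 70% and 21% at a true 60%. It does protect a good protocol: at a true 90% it almost always passes (99.4%).

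The figures assume 18 independent participants in the denominator. They do not model the replacement of children who withdraw during run-in or for unrelated reasons (Premature termination or withdrawal of subjects), or the continuation decision after 10 completers (Interim analysis). The conflict between sizing and rule does not depend on which formula produced 18.

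**What to change.** Keep n = 18 and choose one of two routes:

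1. **Plain progression threshold.** Keep the 70% rule, delete the alpha and power claim, and report the exact 95% interval together with the rule's operating characteristics (go in 53% of trials at a true 0.70, 21% at 0.60, 99% at 0.90). State that a feasible verdict does not show completion above 70%.
2. **A test against 0.7.** Make the decision depend on a named test and print its true properties: at least 17/18 (type I error 1.4%, power 45%) or at least 16/18 (6.0%, 73%), noting that the latter slightly exceeds 5% and that neither reaches 80% power.

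Under either route, rename the endpoint completion rate throughout and correct the abstract.

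The cost is wording in the abstract and in the sample-size, primary-outcome and analysis paragraphs. No extra patients are needed. The first route gives up the claim of a powered test; the second sets a harder bar and shows a less favourable power.

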### Recruitment procedure

Eligible participants will be informed about the study by their treating physician, who will seek consent to contact them for further details. The researcher will then provide the Patient Information Sheet and Consent Form. Participants will have 2 weeks to consider participation, with follow-up calls to answer any questions. If consent is given, the study team will finalise the consent process at the next clinic visit. The age and gender of eligible participants who have been informed about the study but choose not to participate will be registered, along with the reason for not participating, if provided. Recruitment will occur mainly in the outpatient clinic, with additional flyers distributed online and in general practitioners’ offices. Interested individuals can contact the researcher directly. Patients who previously expressed interest in an intervention study during an ongoing survey at Amsterdam UMC will also be contacted.

### Informed consent

In children <12 years of age, informed consent is obtained from parents and verbal assent is obtained from the child. In children ≥12 years, written informed consent is obtained from the parents/guardians and the child.

### Patient and public involvement

The semi-standardised acupuncture treatment protocol in this study has been co-designed in collaboration with acupuncturists in a global network. Prior to the study, a survey was conducted to assess the willingness of children aged 8 years and older with functional gastrointestinal disorders (FGID), as well as parents of children of all ages with FGID, to participate in acupuncture-related research. The survey was anonymous and focused on understanding participants’ readiness to engage in research. While the views of patients and the public have informed some aspects of the study design, no direct patient or public involvement was actively incorporated into the development of this protocol.

### Study schedule

The study lasts 16 weeks, with 10 visits and eight acupuncture treatments.

#### Visit 1: eligibility check (t=−2)

Patients will be assessed for eligibility based on inclusion and exclusion criteria. Baseline data, including anthropometrics, will be recorded. Patients will receive instructions on defecation diaries and escape medication usage. A 2-week baseline run-in period follows, where participants continue PEG treatment (min. 0.2 g/kg/day). Children who meet the modified Rome IV criteria for FC (adjusted for the duration of the run-in period) will be enrolled to receive acupuncture (table 1).^3^

#### Visit 2: screening and first acupuncture treatment (t=0)

After the run-in period, eligibility is confirmed based on the diary information, according to the modified Rome IV criteria. A bowel clean-out regimen (bisacodyl or enemas) is initiated for 2–3 days (box 1). On successful bowel clean-out, the first acupuncture session begins.

Box 1Escape medication
**Bisacodyl**
<11 years of age: 5 mg per dose, once daily (oral/rectal).^*^≥11 years of age: 10 mg per dose, once daily (oral/rectal).^*^
**Sodium docusate (enema)**
6–12 years: 50–120 mL per dose, once daily.≥12 years: 120 mL per dose, once daily.
**Sodium phosphate (enema)**
6–18 years of age: 2.5 mL/kg per dose, once daily (maximum 133 mL/dose).^*^Patients are initially allowed an administration route of choice. However, if 24 hours after oral administration of bisacodyl no defecation has occurred, on the second day, the dose needs to be administered rectally. The third day, an enema is required. Enemas are administered at body temperature.

#### Visit 3–9: acupuncture treatment

Patients receive eight acupuncture sessions over 10 weeks (one per week for 6 weeks, then one every other week for 4 weeks). Acupuncture sessions are conducted by one of two acupuncturists, with a physician or research nurse present. At each acupuncture session, the acupuncturist records the patient’s bowel habits, gastrointestinal symptoms and the use of escape medication during the period between sessions, based on the patient’s symptom diary. At weeks 3, 6 and 10, adverse events (AEs) are evaluated.

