#### Questionnaires and diaries

Patients complete questionnaires on treatment satisfaction, AE, PedsQL and school absence at specified visits. Symptom diaries are maintained daily from the run-in up to the follow-up visit (table 2).

**Table 2 T2:** Study procedures

	T=−2 Eligibility screening	T=0 Screening patient	T=2	T=4	T=6	T=8	T=10	T=14
Research visit (duration in minutes)	X (60)	X (30)		X (30)		X (30)		X (30)
Check for exclusion criteria	X	X						
Informed consent	X							
Rome IV criteria FC assessment	X	X		X		X		X
Acupuncture								
−1 sessions/week			X*	X*	X*			
−1 session/every other week						X*	X*	
Symptom diary	X†	X†	X‡	X‡	X‡	X§	X§	X¶
Adverse events								
Research nurse			X		X		X	X
Acupuncturist		X	X	X‡	X	X‡		
Questionnaires								
Quality of life		X			X		X	X
School absenteeism		X						X
Satisfaction with treatment					X		X	X

* Patients will receive eight acupuncture treatments during 10 weeks (one session per week during 6 weeks, followed by one session every other week during 4 weeks) between t=0 and t=10.

† Patients will fill out the symptom diary daily for the first 2 weeks.

‡ Symptoms over the prior week will be recorded weekly at each acupuncture session.

§ Symptoms over the prior 2 weeks will be recorded fortnightly at each acupuncture session.

¶ Symptoms over the prior 4 weeks will be recorded at the closing session.

FC, functional constipation.

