#### Adverse events

AEs are defined as any undesirable experience occurring to a subject during the study and considered related to acupuncture treatment. Predefined AEs—including needle-related pain, local irritation, haematomas, headache, syncope, sedation and neuropathy—will be assessed weekly via questionnaires. All AEs observed by the investigator or reported by participants will be documented, including severity (mild, moderate or severe) and relationship to treatment (unrelated, possibly, probably or definitely related). Given the nature of acupuncture, serious AEs are not expected.

AEs occurring from the first study-related procedure until 3 months postintervention will be recorded in the case report form and monitored until resolution or stabilisation. Follow-up may require additional tests, medical procedures or referral to a physician or specialist.

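### The treating acupuncturist transcribes symptom data and shares adverse-event recording, and the protocol contradicts itself on whether the daily family diary continues during treatment (minor, cheap to fix)

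*Protocol article*

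**What the plan says.** **Symptom record.** In the protocol article, Visit 3–9: acupuncture treatment states that "the acupuncturist records the patient’s bowel habits, gastrointestinal symptoms and the use of escape medication". This is done at every session, and the family's symptom diary is named as the basis. A little earlier, the same section says that sessions are "conducted by one of two acupuncturists, with a physician or research nurse present".

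**Diary duration.** The text of Questionnaires and diaries has families keep the diary every day from run-in to the follow-up visit. The footnotes to Table 2, in the same section, limit daily completion to the first 2 weeks. For t=2, 4 and 6 the diary row then points to this footnote: "Symptoms over the prior week will be recorded weekly at each acupuncture session". For t=8 and t=10 it points to a fortnightly record made at the sessions, and for t=14 to a record of the prior 4 weeks made at the closing session.

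**Source of the endpoints.** The Efficacy section gives the Rome IV assessment to the investigator and takes the other efficacy endpoints from the diaries.

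**Adverse events.** The Figure 1 caption says "At each session, symptoms and adverse events over the previous week will be recorded", without naming a recorder. Table 2, as extracted, has an AE row headed "Acupuncturist" marked at t=0, 2, 4, 6 and 8, and a research nurse row marked at t=2, 6, 10 and 14. The Adverse events section adds that predefined events "will be assessed weekly via questionnaires". Visit 3–9 places AE evaluation at weeks 3, 6 and 10, and the Safety outcome lists weeks 3, 6, 10 and 14.

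**The concern.** In an uncontrolled, open-label study the before-after change is the only efficacy information. It can be read only if baseline and on-treatment data are collected in the same way. A therapist has an interest in the result, and families may report differently to the person who is needling. If the run-in comes from a daily family diary and the treatment period from a therapist's record at sessions, part of any change could reflect the switch in measurement.

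For safety, the Adverse events section builds relatedness to acupuncture into its definition of an AE. Whoever judges relatedness therefore affects what is counted, and the person delivering the treatment is not the best choice when another clinician is present.

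What is at stake is the secondary information. The Introduction names safety, tolerability and potential efficacy as secondary objectives meant to help design a later randomised trial.

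**Working it through.** The plan gives no figure on this point. Its one calculated figure, the sample size of 18, rests on alpha 0.05, power 0.8 and completion rates of 0.9 and 0.7. None of these depends on who records symptoms. The check is therefore a comparison of passages.

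**Step 1. The two readings of the diary.**

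| Period | If the text governs | If the Table 2 footnotes govern |
|---|---|---|
| Run-in (2 weeks) | Daily family diary | Daily family diary |
| t=2 to t=6 | Daily family diary, transcribed at sessions | Prior week recorded at the session |
| t=8 and t=10 | Daily family diary, transcribed at sessions | Prior 2 weeks recorded at the session |
| t=14 | Daily family diary | Prior 4 weeks recorded at the closing visit |
| Change from baseline to treatment | None in method; the therapist makes a second record | Method and recorder both change |

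The footnotes are passive and name no recorder. The acupuncturist comes from Visit 3–9. That section also says the record is based on the diary, which fits the left column better. The change of recorder therefore arises only if the footnotes are taken literally and combined with Visit 3–9.

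**Step 2. Reach into treatment success.** The end-of-intervention Rome IV assessment covers the last 4 weeks of acupuncture, when sessions are fortnightly (4 / 2 = 2 session records). Under the right column, the symptom data available to the investigator for that window could be those two session records. Under the left column they are the daily diary.

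**Step 3. Adverse events in Table 2, as extracted.**
- Acupuncturist only: t=0, 4, 8.
- Acupuncturist and nurse: t=2, 6.
- Nurse only: t=10, 14.

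The questionnaires come on top of these. The nurse's first AE check is at t=2 in Table 2 but at week 3 in Visit 3–9 and in the Safety outcome, so the two schedules do not match.

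**Step 4. Size.** The documents contain no rate of under-reporting, no agreement figure between diary and session record, and no expected AE rate. The direction of a possible bias can be argued; its size cannot be calculated.

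**The case against.** The case against is strong and much of it stands.

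- **Efficacy.** The acupuncturist is described as working from a family record. The text keeps the diary running to follow-up, the Efficacy section names the diaries as source, and the investigator assesses Rome IV. Endpoints such as the time from acupuncture to defecation presuppose a continuing diary. A reader might infer that the therapist is the source of the efficacy data; the documents do not support that.
- **Safety.** A reader might infer that AE frequency is understated. That would need the therapist to be the main or only channel, and the nurse and the questionnaires are others. The acupuncturist's record can add events. One limit on this defence is that the questionnaire schedule is not uniform: weekly in Adverse events, but surveys at five time points in the Figure 1 caption.
- **Numbers.** One could assume that 20–40% of events go unmentioned and that 12 of 18 children have an AE, giving 12 × 0.8 = 9.6 and 12 × 0.6 = 7.2 children. Neither input is in the documents. The step also fails on its own terms: a child with several events leaves the count only if every channel misses all of them. Nor should 8 − 3 = 5 sessions be read as covered by the therapist alone, since that pairs nurse timing from the text with the acupuncturist row of a table on a different schedule.
- **Benefit.** The physician or nurse is unblinded too, the primary outcome is feasibility, and the Statistical analysis section disclaims efficacy claims.
- **Treatment need.** Point selection in sessions 5–8 depends on persistent Rome IV criteria, so the acupuncturist must know the symptom status. That calls for reading the record, not for being the one who makes it.

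What the objection leaves standing is the contradiction between the text and the Table 2 footnotes, and a therapist in a recording role that staff already present could fill.

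**Conclusion.** The point holds as a minor one. The treating acupuncturist transcribes diary data at every session and is one of two listed AE recorders while a non-treating clinician is in the room. The contradiction over the diary is what gives this weight: under the footnotes, method and recorder both change between run-in and treatment; under the text they do not. The size of any bias cannot be estimated from the documents.

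A reader might also infer a risk to the primary outcome, because repeated need for disimpaction leads to withdrawal and the acupuncturist records escape medication. The protocol does not say that the session record drives that count, so this is not shown.

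The conclusion assumes that the footnotes and AE rows of Table 2 were extracted correctly. A change of recorder would remove only part of the bias, since families and staff remain unblinded.

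**What to change.** 1. Amend the Table 2 footnotes to agree with the text of Questionnaires and diaries, and state that the daily family-completed diary is the source data for all diary-based efficacy endpoints, for the symptom information behind the Rome IV assessment, and for escape-medication use through week 14.
2. In Visit 3–9 and the AE rows of Table 2, have the physician or research nurse already present enter the diary data and collect AEs and their relatedness before each session.
3. Let the acupuncturist read that record for point selection and continue to report events seen during needling, but not act as primary recorder. Removing that report altogether could lose AEs.
4. Reconcile the nurse's AE timing between the text (week 3) and Table 2 (t=2).

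The cost is a few minutes of nurse or physician time per session and an edit to one section and one table. Sample size, alpha and power are unaffected.
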